### Co-interventions and compliance

For participants in the control group, we cannot prevent co-interventions, e.g., recovery therapy or support from job hunters, being offered to them, as these interventions can be part of the SSA’s usual care. For participants in the intervention group, we will ask the SSA team not to offer any additional interventions during the period in which the CS participates in our intervention program. During the follow-up period, after the intervention program in this study has been completed, the SSA team may still offer interventions that are available through usual care. We will monitor any co-interventions offered in both groups by asking questions about this in the questionnaires and, if possible, by data from the participants’ files at the SSA.

### Statistical analysis

All statistical analyses will be performed according to the intension-to-treat principle. If necessary, the per-protocol principle will also be applied [45]. Descriptive analyses will be performed to check whether there are relevant differences in the baseline characteristics of the intervention and the control group at baseline. Analyses will be performed on an individual level. All analyses will be performed both crude and adjusted for potential confounders, e.g., gender, age, stratum of participants, or type of cancer. Also, these variables will be checked for effect modification. Scores on the included outcomes measures and parameters in the study will be calculated according to published scoring algorithms. The results of the questionnaires will be compared between both groups at baseline and at 3, 6 and 12 months follow-up. Correction for baseline values will be applied.

The primary outcome measure, duration until sustainable RTW in both groups, will be described using the Kaplan-Meier method. We will use the Cox proportional hazard model to estimate hazard ratios and corresponding 95% confidence intervals for sustainable RTW. Finally, we will also perform multiple regression analysis to determine associations between the primary outcome measure and predictor variables, such as fatigue and coping strategy, in order to identify prognostic factors for RTW in this population. A two-tailed significance level of <0.05 is considered statistically significant in all analyses. All analyses will be performed using SPSS 20.0 [46].

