**Participant recruitment flow diagram.**

Potentially eligible participants will be recruited using the national database of the SSA, in which persons applying for sickness or disability benefits are registered. The database contains data regarding demographics, employment status, type of sickness or disability benefit and medical cause, due to which the benefits are granted. A search query will be developed to identify CSs with granted benefits due to a cancer diagnosis. An in-house SSA researcher will use the query to identify potential participants, because of privacy concerns. This SSA researcher will only be involved in this particular part of the recruitment process and in no other parts of the study. Retrospectively, the search query will be used only once to identify CSs who have been sick-listed from 12 to 36 months. Prospectively, with a frequency of twice per month, the search query will be used to identify CSs who have been sick-listed for 12 months. Prospective recruitment will continue for an estimated duration of one and a half years, until the sample size will be reached.

Potential participants will receive an information package from the SSA, which will contain an invitational letter from the chief medical officer from the SSA, a brochure with more detailed information on the study, an informed consent form in which respondents can give their consent to be contacted for information regarding the study, and a short questionnaire. The information package will also include a postcard, by which persons can respond to the researcher whether they are interested in the study or they can provide for declining participation, in case they wish not to participate. Also, on the postcard they can select the option of receiving only the baseline questionnaire, which aims to collect data for comparison between responders and non-responders. Finally, if a person is willing to participate, but only after a few weeks or months, they can select ‘contact me later’ on the postcard. Potential participants who do not return either the short questionnaire, including informed consent form, or the postcard, will receive a reminder letter after two weeks.

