### Sample size

As a starting point for calculating the sample size, we chose a Hazard Ratio of 2, indicating that the participants in the intervention group RTW twice as quickly compared to the participants in the control group. This Hazard Ratio is based on comparable studies on RTW of workers who are sick-listed and who are receiving sickness benefits [42,43]. Assuming that half of the workers will achieve sustainable RTW during the first 12 months of the follow-up period, and based on a power of (1-β=) 0.80 and a two-sided significance level of 0.05 (α), a sample size of 130 participants (n = 2 × 65) is needed. Based on comparable research, loss to follow-up of 20% is taken into account. This results in 164 participants (n = 2 × 82) to be included in the study. This number of participants seems feasible as samples from the registration database at the SSA indicate that approximately 3000 persons could be invited for participation over a time period of one and a half year.

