### Randomisation

Prior to randomisation, we will apply pre-stratification in our inclusion procedure to ensure equal representation of the three subtypes amongst CSs with job loss in our sample; (1) workers whose temporary employment contract ended before or during sick leave; (2) temporary agency workers; and (3) unemployed workers. Randomisation to either the intervention group or control group will be performed on the individual level and will be performed separately for each stratum. Randomisation will be performed by the coordinating researchers (with the exception of the executive researcher), using computerized blocked randomisation by means of the Randomisation Plan Generator [44]. The number of participants in each block will be four, with an allocation ratio of 1:1.

Blinding to the randomisation outcome in this study is not possible due to the nature of the intervention program, in which various stakeholders will need to cooperate to support and guide participants in the intervention group. Furthermore, for practical reasons with regard to usual care, the researchers will have to inform the SSA team and the GP of participants about the inclusion of the participant and the group to which the participant was randomised.

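### The primary Cox comparison is run both crude and adjusted for an open covariate list; neither is named primary, and the randomisation stratum is not guaranteed a place in the model

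*Protocol article*

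**What the plan says.** Under Randomisation, the protocol article defines three subtypes of cancer survivors with job loss (ended temporary contract, agency worker, unemployed). It states that allocation "will be performed separately for each stratum", in blocks of four at 1:1.

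Under Statistical analysis, time to sustainable return to work is compared with a Cox model. The adjustment policy for this and every other analysis is: "All analyses will be performed both crude and adjusted for potential confounders, e.g., gender, age, stratum of participants, or type of cancer". The same section plans descriptive analyses to "check whether there are relevant differences in the baseline characteristics of the intervention and the control group at baseline" and sets a two-tailed 0.05 threshold for all analyses. Neither this section nor the abstract says which hazard ratio is the primary result.

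Under Sample size, the design inputs are a hazard ratio of 2, 50% events in 12 months, 80% power and two-sided 0.05, leading to "a sample size of 130 participants (n = 2 × 65) is needed". This is raised to 164 for 20% loss. Covariates play no part in that calculation.

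**The concern.** Two things are fixed badly.

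First, the text commits to two versions of the primary comparison, both judged at 0.05, and does not rank them. The adjusted version is itself a family of models, because its covariates are given only as examples. In an unblinded trial this leaves room to decide after the data are seen which hazard ratio to present as the answer. The two also differ in meaning: the hazard ratio is non-collapsible, so crude and adjusted values need not agree even under perfect balance.

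Second, the analysis does not have to follow the randomisation. The crude model ignores the strata. The adjusted model treats stratum as one possible confounder, although blocking within strata balances it by design. The reason to include it is that it was a design factor, not that it might confound. If stratum predicts return to work and is left out, the standard error is too large for the balance achieved, so the test is conservative and some power is lost.

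**Working it through.** **1. Reproduce the plan's figure.** Inputs from Sample size: "we chose a Hazard Ratio of 2, indicating that the participants in the intervention group RTW twice as quickly", and the assumption that "half of the workers will achieve sustainable RTW during the first 12 months of the follow-up period".

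- Events (Schoenfeld, 1:1) = 4 × (1.960 + 0.842)² / (ln 2)² = 65.35.
- Participants = 65.35 / 0.5 = 130.7, against the stated 130. With 65 events, power is 79.8%.
- Loss: 65 / 0.8 = 81.25, so 82 per arm and 2 × 82 = 164, as stated.

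The sample size reproduces. The formula has no covariate term, so the choice of model does not alter it.

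**2. Simulation set-up.** 130 participants, three equal strata, blocks of four within each stratum, 50% events by 12 months, 2,000 runs per scenario. The models are crude Cox; Cox with stratum as a covariate; Cox stratified by stratum; Cox with all four example covariates (gender, age, stratum, cancer type); and all 2⁴ = 16 subsets of those four. The documents give no prognostic strengths, so these are assumptions shown as a range. The stratum effect is a hazard ratio per step between adjacent strata (2 per step is fourfold between the outer strata). The Monte Carlo standard error is about 0.5 points near 5% and 0.9 to 1.1 points for power.

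**3. No true effect: rejection rate at 0.05 (%).**

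| Stratum HR per step | Other covariates' HR scale | Crude | Stratum-adjusted | Four covariates | Better of crude and four-covariate | Best of 16 |
|---|---|---|---|---|---|---|
| 1 | 1 | 5.4 | 5.5 | 6.1 | 6.8 | 7.6 |
| 1.25 | 1 | 3.9 | 4.3 | 5.1 | 5.6 | 6.7 |
| 1.5 | 1 | 4.3 | 4.8 | 5.9 | 6.7 | 7.4 |
| 2 | 1 | 3.5 | 5.3 | 6.2 | 6.5 | 8.3 |
| 1.5 | 1.5 | 3.9 | 4.5 | 5.3 | 6.5 | 8.6 |
| 2 | 2 | 3.4 | 5.1 | 5.9 | 7.0 | 10.3 |

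Taking the better of two results gives 5.6% to 7.0%. Part of that excess is the four-covariate model's own slight inflation at about 65 events. Relative to that model alone, the choice adds 0.3 points (6.5 − 6.2) to 1.2 points (6.5 − 5.3). The crude test is conservative, at 3.4% to 3.5%, when stratum is strongly prognostic.

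**4. Hazard ratio 2: power (%).**

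| Stratum HR per step | Other covariates' HR scale | Crude | Stratum-adjusted | Stratified | Four covariates |
|---|---|---|---|---|---|
| 1 | 1 | 77.9 | 78.0 | 76.8 | 77.9 |
| 1.25 | 1 | 78.0 | 78.8 | 78.0 | 78.2 |
| 1.5 | 1 | 76.7 | 79.2 | 78.9 | 79.1 |
| 2 | 1 | 73.4 | 79.4 | 78.6 | 78.7 |
| 1.5 | 1.5 | 73.2 | 75.4 | 74.5 | 77.6 |
| 2 | 2 | 63.0 | 69.4 | 68.4 | 76.5 |

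With stratum alone prognostic, crude against stratum-adjusted loses 0.1, 0.8, 2.5 and 6.0 points. Only in the last row, where every covariate is strong, does the gap to the four-covariate model reach 76.5 − 63.0 = 13.5 points; of this, stratum accounts for 69.4 − 63.0 = 6.4.

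**5. Disagreement.** At a hazard ratio of 2, the crude and four-covariate models fall on opposite sides of 0.05 in 5% to 18% of trials, so which one is primary can decide the reported conclusion.

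**The case against.** The strongest reply is that this is a condensed article, and that the final covariate list and the ranking of models commonly sit in an analysis plan that is not shown. That holds for a gap. It does not cover what is written here: two versions of the primary comparison, an open list, one threshold for both, and the design factor offered only as an example confounder. It is also true that the protocol never calls the two results co-primary and does list stratum as a candidate, so there is no outright contradiction with the Randomisation section.

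Three stronger readings are tempting, and the documents do not support them.

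- *The plan loses substantial power by ignoring stratification.* This needs the crude result to be taken as primary, which is not stated, and stratum to be prognostic, for which no figure is given. A scenario with 164 participants and three further assumed covariates gives power of about 73% crude, 77% stratified and 85% fully adjusted. Most of that gain comes from the invented covariates, not from stratification. It also uses 82 events with no loss (Schoenfeld power 88%) instead of the planned 65 or so, so it cannot be set against the planned 80%.
- *Covariates will be picked from observed baseline imbalance.* The baseline check is planned, but the text does not link it to covariate choice. Likewise no search over covariate subsets is described, so the 6.7% to 10.3% range is only what the open wording would permit.
- *Time since sick-listing has been wrongly omitted.* The sample is mixed, since for the retrospective part "the search query will be used only once to identify CSs who have been sick-listed from 12 to 36 months" while prospective recruits are identified at 12 months. That this duration is prognostic is a reasonable judgement, not something the documents show, and an open list does not exclude it.

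Nor is a crude hazard ratio nearer to 1 an error in itself; a marginal effect is a legitimate target if it is the one declared.

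**Conclusion.** The point stands in a limited form. The primary Cox model is not singled out, and the three randomisation subtypes are not guaranteed to be in it. This leaves a choice of result worth up to about 7% false positives instead of 5%. If the crude result is the one used and subtype predicts return to work, the test is conservative and may lose about 0 to 6 points of power at 130 participants and a hazard ratio of 2, and more only if other covariates are strongly prognostic. All these sizes rest on assumed prognostic effects. The sample size of 130/164 is sound and unaffected. This is a free improvement, not a flaw that undermines the trial; confidence is moderate.

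**What to change.** State one primary analysis of time to sustainable return to work: a Cox model stratified by, or including as a covariate, the three randomisation subtypes, with a short closed list of baseline covariates fixed before any outcome data are seen. Age and gender are natural choices. Time since sick-listing at randomisation is optional, and the agency's search already uses sick-listing duration. Label the crude model and any other adjusted models as sensitivity analyses, and say that the primary covariates will not be revised in the light of the baseline comparison.

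Naming one model returns the false-positive rate to that model's own level. In the simulations this was 4.3% to 5.5% with stratum as a covariate and 4.2% to 5.6% stratified. The price is small: if subtype turns out not to be prognostic, stratifying costs about 1 point of power (77.9% to 76.8%), and including it as a covariate costs essentially nothing (77.9% to 78.0%). Only the analysis wording changes; sample size, data collection and trial conduct stay as they are.

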## Discussion

In light of an increasing incidence of cancer and an improving survival rate [47], a rising retirement age [16,48] and a growing number of temporary employment contracts within Western labour markets [17], it is expected that the number of CSs have who lost their job in the working age will increase. CSs with job loss may experience unique challenges in their RTW process, compared to employed CSs, e.g., competition with “healthy” individuals for a job, lack of a workplace to return to and lack of social support from colleagues or an employer. Therefore, they may be in need for a tailored approach for RTW. This study aims to evaluate the effectiveness of a tailored RTW intervention program on duration until sustainable RTW of CSs with job loss, compared to usual care.

### Methodological considerations regarding the study design

There are several methodological aspects of this study that can be considered. One of the main strengths of this study is that, in the developmental process of the tailored RTW intervention program, we have incorporated (1) ideas and perspectives of a large variety of stakeholders in the fields of cancer, work and insurance medicine in the Netherlands, (2) results from previous international studies on RTW for CSs, and (3) results from a qualitative focus group study on barriers and facilitators for RTW in CSs with job loss. Another strength of this study is that we will evaluate the effectiveness of the tailored RTW intervention program with a RCT design, and that we will conduct a process evaluation alongside the RCT. Furthermore, the procedures for this study were developed in accordance with the Dutch SSA. This will facilitate implementation of the study protocol, particularly the recruitment protocol, at the SSA.

There are also several limitations to be considered with regard to the study design. First of all, this is the first study to be conducted that incorporates a RTW intervention for CSs with job loss. Therefore, in developing the tailored RTW intervention program, we had to rely on indirect evidence from studies on RTW for employed CSs, and adjust this information, taking into account our knowledge of the situation of CSs with job loss, which is a subjective process. We did not take other intervention studies on RTW in persons with chronic diseases (other than cancer) into account in developing the tailored RTW intervention program. Still, the tailored RTW intervention program is based on elements of the attitudes-social influences-efficacy model [24], which indicates that there is, to some extent, a scientific basis for the content of the program.

Ideally, this study design would have incorporated a pilot phase, in which we could evaluate whether the intervention program would be acceptable and sufficiently tailored to the needs of CSs with job loss. In addition, a pilot study would have enabled us to discover potential implementation problems for the intervention program beforehand and to evaluate whether or not the chosen recruitment strategy for the RCT would be feasible and successful. Unfortunately, we were not able to carry out a pilot phase in this study.

With regard to the sample size, we chose a Hazard Ratio of 2, which is not uncommon for studies in (moderately) comparable populations. Still, this number might be optimistic in terms of the anticipated results. Another limitation is that this study does not use blinding, i.e., we have to disclose to the participant’s RTW team at the SSA whether the participant is in the intervention group or the control group. This could potentially lead to awareness in the SSA teams about their care being evaluated, which could result in a different type of usual care provided to the intervention group compared to the control group. Finally, blinding could prevent contamination of the control group, but as this study recruits 82 participants for the intervention group on a national level, the researchers estimate the risk of contamination of the control group marginal. Potentially, increased awareness of RTW could lead to participants in the control group employing RTW activities on their own, which they might not have done if they were not participating in the study. Enhanced RTW activities in the control group could distort a potential effect of the tailored RTW intervention program and lead to an underestimation of any effect that will be measured between the intervention group and the control group. Finally, it is not unlikely that CSs with job loss feel disappointed in the labour market (due to job loss) or the social security system (due to a lack of appropriate RTW interventions), which may influence their willingness to participate in an experimental study that offers a RTW intervention program. This could potentially lead to selection bias in our sample of participants.

### Implications of study findings for research

The results of this study will contribute to the literature by providing insight into the RTW process of CSs with job loss and the ways in which RTW can be facilitated for them. In a broader perspective, the results of this study may change the way the RTW process of CSs is generally studied. To this day, the literature on RTW does not distinguish CSs based on work-related factors, such as working status or type of employment contract, but rather distinguishes CSs on medical factors, such as type of diagnosis. If the results of this study demonstrate a positive effect in favor of a tailored approach for CSs with job loss, then opportunities may be created to develop future RTW interventions tailored to work-related factors, e.g., employment status, present in CSs. Possibly, this approach may also be applied to persons with job loss with other (chronic) conditions, in order to facilitate their RTW.

### Implications of study findings for practice

This study may demonstrate that it is effective to tailor RTW support for CSs to work-related factors, such as employment status, at least in Western economy countries. If so, policymakers should find ways to implement tailored RTW intervention programs for CSs with job loss. This study may also have a positive impact on the increasing burden of sickness and disability benefits. As more CSs may return to work as a result of a tailored RTW intervention program, the number of CSs receiving benefits will decrease. As benefits are indirectly provided by the tax payers in Western economy countries, society as a whole could potentially profit from a higher number of CSs returning to work.

### Conclusion

There is a gap in the literature regarding the RTW process of CSs who have lost their job. We hypothesize that CSs with job loss benefit from a tailored approach regarding RTW support, as a result of unique challenges, e.g., lack of a current job, going through job application processes, competing with “healthy” individuals for a job and having a large emotional and practical distance to the labour market. This study aims to facilitate sustainable RTW for CSs with job loss, by offering a tailored RTW intervention program and evaluate its effectiveness compared to usual care. Results of this study will be available in 2016.

## Abbreviations

CS(s): Cancer survivor(s)
GP: General Practitioner
RCT: Randomized controlled trial
RTW: Return to work
SSA: Social security agency
VUmc: VU University Medical Center
